### Participants

From the units participating in the CRCT we have the following main categories of participants: Patients, next of kin, health care personnel and implementation teams, including health care professionals and unit leaders. These will be recruited from the units to take part in both the quantitative and qualitative studies. Furthermore, we will study barriers and facilitators qualitatively in a wider context, including stakeholders from other health care services, and from the municipal, regional, and national level. An overview of the respondents and sub-studies is presented in Table 1, and each sub-study is described below.

**Table 1 Tab1:** An overview of the sub-studies and respondents in the Norwegian ACP trial

ACP sub-study	Respondents	Number	Time of data collection	Type of data
**Implementation outomes**				
Fidelity measurements	Health care personnel, resource persons, leaders in the hospital units	All 12 participating units	Baseline, 7-10 and 18 mos	Fidelity assessments

**Qualitative studies in a wider context Barriers and facilitators**				
The wider health service context	Health care personnel and chief physicians in hospitals and community services	40 respondents	Baseline	Individual and focus group interviews
National, regional and municipal level	Health politicians, health authorities, health administrators, professional- and user organizations	15 respondents	Baseline-8 mos	Individual interviews
**Health economics**				
Health economic analysis	Information from participating units Patients and next of kin	All 6 intervention units	0-18 mos 13-18 mos 18 mos. Pre-18 mos. post inclusion	Cost data Data from triadic study including health registry data (see above)

### Patients and next of kin

Patients and next of kin will be included by local health care personnel, led by the local research coordinator. In the quantitative triadic sub-study, patients and one close relative will be asked to participate together with the attending clinician in both the intervention and in the control arm (see below). In the qualitative sub-studies, patients and next of kin from the intervention units having experience with ACP will be invited to participate. Inclusion- and exclusion criteria for patients and next of kin in the triadic sub-study is described below. For the qualitative sub-study, we use similar criteria with some adaptations.

#### Inclusion criteria for patients

Home-dwelling70 years or olderAcutely admitted to the participating unitSufficient language proficiency in Norwegian to respond to the questionnaireClinical frailty score of 4 or moreThe physician responsible for the patient's medical care answers "no" to "Surprise question" from Gold Standards Framework proactive identification guidanceBoth patient and a close relative (preferably the closest relative) would participate in ACP together if offeredBoth patient and the close relative consent to participate in the research project

#### Exclusion criteria for patients

The patient is not competent to consent to research participationThe patient is expected to die within 24 hThe patient has participated in ACP prior to the current hospital admissionIn the intervention armoACP is not conducted with patient, a close relative and physician before hospital dischargeoThe clinician that participated in the ACP conversation has not consented to research participationIn the control armoThe patient or the relative would not have been able to participate in ACP during hospitalizationoAn attending clinician has not consented to research participation

#### Inclusion criteria for next of kin

A close relative of a patient who fulfill all inclusion criteria and no exclusion criteria; and who would be willing to participate in ACP together with the patient if offered18 years or olderSufficient language proficiency in Norwegian to answer the questionnaireBoth patient and the close relative consent to participate in the research project

#### Exclusion criteria for next of kin

The relative is not competent to consent to research participation

### Health care professionals and local unit leaders

Health care personnel will have many roles in the implementation, the ACP intervention, and the research in this study. According to the whole-ward approach, the project encourages the units to include all clinicians in the ACP training, and some will actively participate in the clinical intervention, by providing ACP as a part of the clinical care. Dedicated clinicians will be appointed to roles as ACP-coordinators and implementation teams, thereby performing tasks related to both implementation and research. The implementation teams consist of clinical staff with a special interest or expertise relevant to ACP, and the closest leader. In Norwegian hospitals, the local unit leaders are in general health care professionals using some or all their time to lead the unit or a part of the unit. A research coordinator will be responsible for recruiting patients and next of kin to the quantitative and qualitative studies in collaboration with the staff.

The study will collect data from the health care personnel in four sub-studies: The fidelity assessments, a quantitative study to all health care personnel and the unit leaders, and the triadic study including an attending clinician, in both the intervention and the control arms, and qualitative interviews with ordinary clinicians and with the implementation teams in the intervention units.

In the triadic sub-study, the participating clinician will also provide clinical data about the included patient. This participating clinician should be closely involved in the health care provided to the patient during the hospitalization and have sufficient knowledge of the patient’s health and health care needs. If feasible, the participating clinician will be the attending clinician responsible for the patient’s medical care. In the intervention arm, the participating clinician should also be the clinician who participated in the ACP.

### Stakeholders in a broader context

Two qualitative sub-studies include selected stakeholders to explore barriers and facilitators for ACP in a broader context. The first, already published, explores barriers and facilitators in a wider health care service context and includes health care professionals and chief physicians in hospitals and in municipalities [53]. The second explores barriers and facilitators at the municipal, regional and national level. In this study we include stakeholders who are relevant to health care policymaking: health politicians on a national level, national health authorities, high-level leaders in both the hospital and municipal health care system, professional associations, user- and interest organizations, as well as leaders of health care educations.

### Blinding

Due to the nature of the project, neither the units, the local leaders, the health care personnel nor the project’s researchers can be blinded to the hospital units’ allocation status. The project group is small, and the project’s researchers will contribute to all parts of the project, including developing the implementation program and providing the implementation support. This makes the researchers more familiar with and knowledgeable of all aspects of the units, which strengthens the tailoring of the intervention, and it improves the quality of the evaluation. On the other hand, having researchers evaluate the results of a program and the support they have provided themselves may lead to a risk of experimenter bias. This will be minimized by awareness of the risk of bias and by dividing the responsibility for the implementation and for the evaluation between different researchers. To prevent selection bias, patients and next of kin will not be informed about the hospital unit’s allocation status, but they may deduce this from the kind of treatment they receive. We assume that self-reported data and data collected from national registries to a low degree will be susceptible to bias.

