### The ACP interventions

The ACP interventions in this study, combining implementation strategies, an implementation intervention and the clinical intervention ACP, were developed by the project group. It is building upon research at CME on end-of-life ethics, patient involvement, decision making processes for older patients and their next of kin and ACP in nursing homes in Norway, and national and international research and guidelines on ACP and end-of-life decision-making.

The ACP interventions consist of the following elements (described in detail in Additional file 2).I Clinical intervention: advance care planning1.1 Routine identification, information and invitation to ACP to all eligible patients and next of kin.1.2 ACP conversations routinely provided to all consenting patients and their next of kin.1.3 Documentation and collaboration with other health care services and levels.II Implementation intervention2.1 Implementation team.2.2 ACP coordinator.2.3 Training and supervision: Kick-off, training of resource persons and health care personnel including practical exercises, monthly contact with units, network meetings.2.4 Toolkit and shared resources: ACP guideline, pocket card, teaching material, information leaflets, documentation templates etc.2.5 Structured fidelity measurements of the implementation level of a) the implementation interventions and b) the clinical intervention, with tailored feedback and supervision.2.6 Evaluation of the intervention and implementation.III Implementation strategies3.1 Ensuring leadership commitment.3.2 Responsive evaluation.3.3 Whole ward approach.3.4 Train the trainer model.3.5 Sustainability after the project.

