#### Data collection

We defined baseline as the situation before the start of the intervention, and the baseline fidelity measurements were conducted from May to August 2022. The participating hospital units were randomized to the intervention- or control arm after the baseline fidelity measurement in August 2022. The implementation period started with kick-off on Oct 25th, 2022, and will continue for approximately 18 months (when the inclusion for the triadic sub-study is completed, and before the last measurement of fidelity). Fidelity measurements in the intervention arm will be at baseline, at 7–10 months after the start of the intervention (May to August 2023) and at 18 months (April 2024). Fidelity measurements in the control arm will be at baseline and at 18 months. The second fidelity measurement is not done in the control group due to resource considerations, and to avoid influencing clinical activity in the control arm.

The fidelity scores at each unit will be based on a) interviews with leaders, b) interviews with resource persons, c) interviews with physicians, d) interviews with nurses, e) written material (e.g., information brochures or clinical procedures) and f) existing routine data (number of patients eligible for/offered/received ACP). Seven of the project members participate in the data collection, forming teams of two people visiting each site. Based on the interviews and available information, the two researchers will, at the end of the visit, score fidelity individually, and subsequently discuss possible discrepancies and decide on a consensus score.

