### Clinical effectiveness – The triadic sub-study with patients, next of kin and clinicians

In this sub-study, we will assess and compare ACP relevant outcomes between the intervention arm and control arm. As described, we use a triadic approach, by recruiting each patient together with a close relative, and an attending clinician. This allows us to assess and compare the perspectives of all three stakeholders across the two study-arms. We aim to include at least 420 triads in total from the two arms. Each person in each “triad” will complete a questionnaire inspired by past ACP-, end-of-life- and shared decision-making studies and adapted to the Norwegian context and the current study. Paper questionnaires will be used for patients, the next of kin can choose between paper and digital questionnaires and digital questionnaires will be used for the clinicians. The patients will be offered assistance in filling out the questionnaire by a staff not involved in the treatment of the patient. The inclusion of participants will start approximately 13 months after the start of the intervention in the implementation arm.

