#### Recruitment

A local research coordinator at each participating unit will recruit participants assisted by the health care personnel at the units, guided by a set of instructions and supervision by the researchers. All potential participants will be assessed for eligibility. The patients who fulfil the criteria will receive verbal and written information about the study from a health professional at the unit. If a written informed consent is obtained, the health professional will ask the patient for permission to contact the closest relative to inform and possibly obtain consent and include him or her, and subsequently inform and recruit the clinician. The patient, the next-of-kin and the clinician will be included if the whole triad consents to participate. At the time of submission of this manuscript, the units were just about to begin recruiting participants to the triadic sub-study.

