#### Data analysis

Demographic and clinical data about the patients will be used to assess whether the patients in the control and intervention units are comparable. In addition, the participating units will collect basic and anonymous clinical information about all patients admitted to the units at shorter random time periods, to get more information about the participant units and to compare the included patients with all admitted patients.

Number and percentages of invitation to and participation in ACP for patients and next of kin will be calculated and compared between intervention and control group. The primary statistical analyses will be the difference in mean outcomes between participants in the intervention and the control group using linear mixed effects models. The random part of the model will consist of random intercept for patient or relative identification nested within centre. Missing data will be handled by multiple imputation using predictive means matching with 100 imputed data sets.

If the analyses show differences in the intervention and control arm, we will perform analyses to assess if higher fidelity score (higher levels of implementation) is associated with improved outcomes for patients, next of kin, and clinicians. For the secondary outcomes, we will compute average outcomes and SD for the intervention and the control group and use the t-test to determine if there is a significant difference between groups.

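### Withholding allocation from patients cannot prevent identification bias when unblinded unit staff select triads after randomisation, and the stated triadic model names no patient covariates to offset a case-mix difference.

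*Protocol article*

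**What the plan says.** All places are in the protocol article.

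- **Timing.** Under the fidelity outcome's Data collection heading, the units "were randomized to the intervention- or control arm after the baseline fidelity measurement in August 2022", with kick-off on 25 October 2022. For the triadic sub-study: "The inclusion of participants will start approximately 13 months after the start of the intervention in the implementation arm".
- **Who selects.** Recruitment: "A local research coordinator at each participating unit will recruit participants assisted by the health care personnel at the units". Blinding: "neither the units, the local leaders, the health care personnel nor the project" researchers can be blinded.
- **Entry criteria.** Besides age, residence, acute admission and frailty, the inclusion criteria need the responsible physician's negative answer to the surprise question, and a patient and relative who would join ACP if it were offered. The exclusion criteria differ by arm. An intervention patient drops out if ACP was not held before discharge. A control patient drops out if judged unable to have taken part.
- **Link to the intervention.** The first clinical element is "Routine identification, information and invitation to ACP to all eligible patients and next of kin". On training, "the project encourages the units to include all clinicians in the ACP training".
- **Safeguard.** "To prevent selection bias, patients and next of kin will not be informed about the hospital" unit's allocation. The same sentence concedes that participants may work it out from their care.
- **Use of patient data.** In the triadic Data analysis section, demographic and clinical data "will be used to assess whether the patients in the control and intervention units are comparable". Anonymous data on all admissions in random periods allow a comparison with the included patients. The primary analysis is a difference in means from a linear mixed model; its random part is described and no patient covariate is named. The Health economics section adjusts its cost regression for age, gender, comorbidity and other characteristics.

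**The concern.** In a cluster trial that enrols individuals after allocation, randomisation balances the units but not the patients whom staff choose to put forward. Here the staff who choose know their arm, and part of the choice is a prognostic judgement. In one arm, finding candidates for ACP is an activity the trial sets out to change. If the two arms put forward patients at different stages of decline, or families differently disposed to talk about it, then communication ratings, clinician congruence and later service use could differ without any effect of ACP.

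The one measure labelled as preventing selection bias acts on patients and relatives, not on those who identify and approach them. A comparability table may show an imbalance, but it does not remove it from the estimate.

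**Working it through.** **Chain of selection**

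1. Randomisation was in August 2022. Month 13 after the October 2022 kick-off is about November 2023, roughly 15 months after allocation. Every triad is therefore chosen with the allocation known to the unit.
2. Two inclusion criteria are judgements (surprise question, hypothetical willingness). One exclusion is an observed event in the intervention arm (ACP held or not) and a hypothetical judgement in the control arm.
3. Withholding allocation can act at the consent step. It cannot act at the earlier steps of identification and approach, which staff carry out.

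The first two steps make a case-mix difference possible. They do not show that one occurs.

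**The plan's own sample size**

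Inputs from the section on selection, allocation and sample size: 0.5 SD, ICC 0.05, 80% power, 95% certainty (taken as two-sided 5%), 22 per cluster, six clusters per arm.

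- Individually randomised n per arm: 63 (normal) or 64 (t-test).
- Design effect: 1 + (22 − 1) × 0.05 = 2.05.
- 63 × 2.05 = 129.2; 64 × 2.05 = 131.2. At 22 in each of six clusters this becomes 132, as stated.

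The sample size is not at fault.

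**Illustration of what a selection shift would do**

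At the recruitment target of 35 per cluster:

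- SE of the arm difference = √[(2/6) × (0.05 + 0.95/35)] = √(0.3333 × 0.0771) = 0.160 SD.
- Assume no true effect and a selection-induced outcome shift b. Test at two-sided 5% with a noncentral t on 2 × 6 − 2 = 10 df.

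| Assumed b (SD) | b / SE | False-positive rate |
|---|---|---|
| 0 | 0 | 5.0% |
| 0.10 | 0.62 | 8.7% |
| 0.20 | 1.25 | 20.4% |
| 0.30 | 1.87 | 39.4% |

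One way to picture b is the arm difference in the share of some patient subtype times that subtype's effect on the outcome (both assumed). A difference of 0.1 in share with an effect of 0.3 SD gives b = 0.03 and 5.3%. A difference of 0.2 with 0.5 SD gives b = 0.10 and 8.7%. A difference of 0.3 with 0.8 SD gives b = 0.24 and 27%. So the consequence runs from negligible to serious.

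More patients per unit do not help: at b = 0.20 the rate is 17.7% with 22 per cluster and 20.4% with 35.

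**The case against.** The strongest reply has five parts.

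- **The article is condensed.** It names a mixed model and its random part; it neither lists nor rules out fixed covariates, and an unseen analysis plan may add them. This stands. A reader might infer that the plan forbids adjustment, but the document is only silent. What remains is that the stated use of patient data for these outcomes is a comparability check, while the article does name covariates for the cost regression.
- **Patient data are not used solely for comparability.** A reader might infer that they are, from the triadic section alone. The Health economics section shows otherwise, so the point is confined to the triadic effectiveness outcomes.
- **Training is encouraged, not required.** A reader might infer that every intervention physician has had a year of training in spotting candidates. The article does not say so, and details sit in an additional file that is not shown. The point does not need it: routine identification is a listed element of the intervention.
- **Mitigations exist.** All potential participants are assessed for eligibility, recruiters have instructions and supervision, project members monitor recruitment, several criteria are objective, and included patients are compared with all admissions. These can limit or reveal imbalance. They do not blind selection or correct the estimate.
- **The shifts are assumed.** If measured case mix correlated 0.2 with the outcome, a 0.20 SD outcome shift would need a 1 SD difference in case mix (0.20 / 0.2). That is a fair caution against leaning on the larger figures.

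The safeguard sentence can also be read as concerning only participants' own choice. On that reading it is reasonable but covers one route to selection bias, and the wording does not say so.

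**Conclusion.** The point holds within limits. The Blinding section credits a measure with preventing selection bias when it cannot reach the people who select. Post-randomisation identification by unblinded staff, judgement-based entry and arm-specific exclusions leave the triadic comparison open to a case-mix difference, and the stated primary model contains nothing that would offset one.

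The documents do not show that such a bias will occur, which way it would run, or how large it would be. The rates of about 9% and 20% follow from assumed shifts of 0.10 and 0.20 SD, with the plan's ICC and cluster numbers, and should be read only as illustrations. The fidelity outcome, which is analysed at unit level, is not affected. The change is worth making because it is cheap, not because a defect of known size has been shown.

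**What to change.** 1. **Blinding section.** State that those who recruit know the allocation, that identification bias is possible, and that supervised screening and the comparison with all admitted patients limit it only in part. Confine the claim about withholding allocation to participants' own decision to take part.
2. **Recruitment instructions, both arms.** Record age, Clinical Frailty score and the surprise-question answer at admission screening, before ACP is raised, and approach eligible patients in order of admission.
3. **Triadic analysis.** Fit the primary models with fixed terms for age, sex and Clinical Frailty score at enrolment, and give the unadjusted result as a sensitivity analysis. Report the selected fraction by arm, using the screening records and the random-period data. The surprise-question answer cannot be a covariate, because every enrolled patient has the same one.
4. **Limitations.** State the arm-specific exclusions openly; none of the above removes that asymmetry.

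**Cost.** Some screening work at 12 units, which were about to start recruiting when the article was submitted. Age and frailty are already needed for eligibility, and gender is already listed for the cost regression. Three patient-level terms are a small burden with 420 patients. Adjustment removes measured differences only, and frailty is itself scored by unblinded staff, so it may carry some of the same differential judgement.
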